### Laboratory procedures

After signing the Informed Consent Form (ICF) and undergoing eligibility assessment for study participation (including CXR, Xpert MTB/RIF Ultra and TB symptoms checklist), participants will undergo a baseline visit, followed by blood collection for Standard F TB and QFT tests. Subsequently, all participants will receive an injection of Cy-Tb (figure 1).

**Figure 1 F1:**
[figure not shown]
Diagnostic accuracy study overview. QFT-Plus, QuantiFERON-TB Gold Plus; Standard F TB, STANDARD F TB-Feron FIA; TB, tuberculosis.

The CXR will be assessed by a single radiologist in the imaging department according to clinical routine and will be done prospectively and directly. The radiologist will be blinded to the Xpert MTB/RIF Ultra results.

10 mL of blood will be collected to three Standard F TB Tubes (Nil, TB Ag and the mitogen tube, 1 mL each tube) and four QFT-Plus tubes (Nil; TB1; TB2; Mitogen) for each participant, whereby the tubes will be incubated at the temperature of 37°C for a period of 16–24 hours. Standard F TB will be processed using the STANDARD F2400 equipment (SD Biosensor), an automated device. The ELISA test will be performed on QFT-Plus tubes. All tests will be processed and performed at the Vietnam National Reference Lab (VNRL)—National Lung Hospital. After being collected at the outpatient department at the same hospital, study samples will be transported to VNRL within 2 hours while still fresh. Lab personnel interpreting Standard F TB test results will be blinded to all other test results.

After blood collection, all participants will receive an intradermal injection of Cy-Tb and the results will be read after 48–72 hours. A solitary test dose of 0.1 mL comprises 0.05 µg each of rdESAT-6 and rCFP-10. These components elicit a delayed-type hypersensitivity reaction mediated by T lymphocytes. In individuals with previous mycobacterial exposure, this reaction results in induration at the injection site typically appearing within 48–72 hours, similar to the TST.^9^

In order to ensure the blinding of Standard F TB results to the reference test (QFT-Plus) and comparator test (Cy-Tb) and to the result of the microbiological reference standard including Xpert Ultra, different operators will be assigned and will be instructed to record results independently of other test results. Cy-Tb will be interpreted by a trained study nurse in the outpatient department.

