Simplified versions of IGRAs are emerging,^11^ including the lateral flow Standard F TB assay (SD Biosensor, Gyeonggi-do, Republic of Korea). Standard F TB has fewer manual processing steps than current-generation IGRAs. After incubation for 16–24 hours, the results will be available in 15 min. Following the stimulation with ESAT-6 and CFP-10 antigens, the IFN-γ production in whole blood is measured by a fluorescent immunoassay.^12^ A recent clinical trial comparing the sensitivity and specificity of the Standard F TB versus QIAreach QuantiFERON-TB (QIAGEN, Venlo, The Netherlands), using TST as a reference standard, showed that the Standard F TB has 88.9% sensitivity and 92.5% specificity for TB infection diagnosis.^13^ However, given the limited accuracy of TST in diagnosing TB infections, further studies comparing to the current gold standard are warranted. Compared with QFT-Plus, the Standard F TB assay may offer important advantages, such as being able to be implemented in low-resource settings, and reducing the financial burden on health systems and people with TB. The Standard F TB assay is currently undergoing Expert Review Panel for Diagnostics and WHO review.^14^

Currently, there are no studies comparing the accuracy of Standard F TB versus QFT-Plus. In addition, there are also no head-to-head comparisons of the sensitivity and specificity of Cy-Tb and Standard F TB. The studies comparing the accuracy of Cy-Tb test versus QFT-Plus have been conducted in Spain and South Africa,^9 15^ whereas there are no studies in a high TB burden, Asian population. This study was designed to address these knowledge gaps.

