### Study benefits, costs or payments

#### Study benefits

There is no known direct benefit to participants for being in this study. The anticipated future benefit is improved diagnostics of TB infection. All participants who test positive on the QFT-Plus test will receive TB preventive treatment in accordance with the guidelines established by the Vietnam National Tuberculosis Programme.^7^

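### Cy-Tb, the index test read by a person, has no stated masking to the blood results or study group, and the plan lets it be read after those results can exist

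*Protocol article*

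**What the plan says.** The Abstract, Main objective and Endpoints of the protocol article treat Cy-Tb and Standard F as two index tests of equal standing, both judged against QFT-Plus.

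The Laboratory procedures section (text under Figure 1) then sets out a blinding scheme:

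- On Standard F: "Lab personnel interpreting Standard F TB test results will be blinded to all other test results".
- On purpose: "In order to ensure the blinding of Standard F TB results to the reference test (QFT-Plus) and comparator test (Cy-Tb"), and also to Xpert Ultra. Here Cy-Tb is labelled a comparator.
- On means: "different operators will be assigned and will be instructed to record results independently of other test results".
- On Cy-Tb: "Cy-Tb will be interpreted by a trained study nurse in the outpatient department". Nothing is said about what the nurse may know.

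The only other masking is that of the radiologist to Xpert, which concerns eligibility. No masking is stated for the QFT-Plus operators.

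On timing, blood is drawn first and "the tubes will be incubated at the temperature of 37°C for a period of 16–24 hours". Afterwards "all participants will receive an intradermal injection of Cy-Tb and the results will be read after 48–72 hours". Standard F is run on an automated instrument.

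**The concern.** An induration is judged by a person. A reader who knows the IGRA result, or knows that the participant has confirmed TB or was selected for a past negative IGRA, can be drawn towards the expected answer when the reading is borderline. The written protection sits on the automated assay, and the human-read test has none of its own.

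The primary and secondary endpoints are accuracy estimates for both tests, and the article presents the study as their first simultaneous comparison against QFT-Plus. A pull on one test only would make Cy-Tb look closer to QFT-Plus than it is and would alter its standing relative to Standard F. More participants would not remove such a bias, and nothing in the planned analysis would reveal it.

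**Working it through.** **Step 1. What the plan quantifies.** The plan gives no figure for this issue. The relevant planning values, from Sample size, are sensitivity 75.8% (Cy-Tb) and 88.9% (Standard F), and specificity 98.1% and 92.5%. As a check that 75.8% is the value actually used: 1.96² × 0.758 × 0.242 / 0.1² = 70.5, which rounds up to the stated 71 for Group 1.

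**Step 2. Who is masked to what.**

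| Test | Read by | Stated masking |
|---|---|---|
| Standard F | laboratory staff, automated device | to all other test results |
| QFT-Plus | laboratory, ELISA | none explicit; separate operators, independent recording |
| Cy-Tb | outpatient nurse | none explicit; separate operators, independent recording |

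**Step 3. Can blood results exist before the Cy-Tb reading?** Inputs are transport up to 2 h, incubation 16–24 h (Laboratory procedures), and a Standard F read time of 15 min (Background: "After incubation for 16–24 hours, the results will be available in 15 min"). With transport at its full 2 h:

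- Earliest Standard F result: 2 + 16 + 0.25 = 18.25 h after the draw.
- Latest: 2 + 24 + 0.25 = 26.25 h.
- Margin to the earliest Cy-Tb reading: 48 − 26.25 = 21.75 h.

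The injection follows the draw, so the true margin is slightly longer. QFT-Plus tubes leave incubation by about 26 h. The ELISA duration and any batching are not stated, so a QFT-Plus result before 48 h is possible but not certain.

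**Step 4. Illustrative size if the reader knows QFT-Plus.** Let f be the share of Cy-Tb readings discordant with QFT-Plus that are read as concordant. The documents give no value for f; 10–20% is an assumption.

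- Sensitivity = 0.758 + 0.242f. At f = 0.10 this is 0.782, and at f = 0.20 it is 0.806, a rise of 2.4 to 4.8 points.
- Specificity = 0.981 + 0.019f. The rise is 0.2 to 0.4 points.
- Planned gap to Standard F in sensitivity: 88.9 − 75.8 = 13.1 points. It would shrink to 10.7 (88.9 − 78.2) or 8.3 (88.9 − 80.6), closing about 18–37% of it. The two planning values rest on different cited sources, so this gap is only a yardstick.

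**Step 5. If the reader knows only Standard F.** The pull is then towards Standard F, and the same model gives 0.758 + f × (0.889 − 0.758). The rise in sensitivity is 1.3 to 2.6 points. Specificity changes by f × (92.5 − 98.1), a fall of 0.6 to 1.1 points. The effect on sensitivity is smaller, but this is the result whose availability is clear from Step 3.

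**Step 6. Study group.** The Data analysis plan also defines sensitivity in Group 1 and specificity in Group 3. There, knowing the group is enough to suggest the expected answer, without any blood result. The document gives no basis for putting a number on this.

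**The case against.** The strongest reply is that the nurse is already covered. The instruction on different operators is not limited to Standard F staff, and the sentence directly after it names the nurse, so she can fairly be read as one of those operators. This stands in part: a reader might infer that Cy-Tb is left wholly unprotected, and the text does not support that. But the instruction governs who records and how. Its stated aim is to protect Standard F, and recording independently is not the same as not knowing.

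Second, no route from laboratory to nurse is shown. The blood tests are run at the reference laboratory and the skin test is read in the outpatient department. A reader might infer early return of results from the Study benefits statement that "All participants who test positive on the QFT-Plus test will receive TB preventive treatment". That sentence gives no timing and does not mention the nurse. The Safety considerations section says test results will not guide care. The two statements need reconciling, and neither establishes when results reach the clinic. This objection stands: exposure is permitted, not demonstrated.

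Third, the illustrated shift lies inside the planned precision of 0.1 and rests on an assumed f. Both are true. Precision describes random error, however, and a systematic shift in one of two compared tests is not absorbed by it.

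Finally, release rules often sit in a full protocol or operating procedures, which are not shown. If they already mask the nurse, one sentence here settles the matter. The article does not omit blinding, though: it sets out a scheme, and that scheme is one-sided.

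**Conclusion.** The point holds as a gap in the blinding scheme. Explicit masking is given to the Standard F readers only. The Cy-Tb reader has at most an indirect instruction that does not keep blood results or study group from her. The stated timings put the reading at least about 22 h after a Standard F result can exist, and possibly after a QFT-Plus result. The plan therefore permits review bias, mainly upward in Cy-Tb sensitivity and in its comparison with Standard F.

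The size is not derivable from the document. Under an assumed 10–20% flipping of readings discordant with QFT-Plus, sensitivity would move from 75.8% to 78.2–80.6%. The effect on specificity is negligible, so a claim that both accuracy measures would be materially inflated is not supported. Nor does the document show that the nurse will in fact see the results, or that QFT-Plus results will be ready in time. The change is worth making because it is cheap and the bias could not be corrected afterwards.

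**What to change.** In Laboratory procedures, extend the blinding rule to Cy-Tb and name it as an index test rather than a comparator:

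- State that the Cy-Tb reader is masked to QFT-Plus and Standard F results and, where practical with existing staff, to study group.
- Require the induration to be recorded and locked in the eCRF before any QFT-Plus or Standard F result is released to the outpatient department.

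No sample size changes. The cost is a release rule in the existing eCRF and a later arrival of blood results in the clinic. Standard F results would be held for about 22 h (48 − 26.25) to about 54 h (72 − 18.25), so up to about two days. Masking to study group may not be fully achievable if the same nurse meets participants at enrolment, hence the qualifier.

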### Safety

Adverse reactions to intradermal injections will be recorded and managed by the treating clinicians according to local treatment guidelines or standard algorithms. Guidance on the management of specific adverse reactions will be provided in a clinical management guide. The most common side effects of Cy-Tb are mild reactions at the injection site, for instance, itching and pain (23.7%–53.1%).^19^

### Endpoints

#### Data collection

Data on age, sex, demographics (occupation, residence, education level, living situation) body mass index (BMI), TB symptoms, TB exposure and previous TB disease or TB infection, and comorbidities (diabetes, immunodeficiency status, organ transplantation, etc) will be acquired through a preformed questionnaire during study visits. These data will be self-reported by participants and supplemented, where available, from the national TB registry and medical records. To assess immunodeficiency status, we will conduct thorough evaluations of participants’ medical history, including any known immunocompromising conditions such as HIV/AIDS, autoimmune diseases, malignancies or history of organ transplantation as well as the use of immunosuppressive medications like biologics, infliximab or checkpoint inhibitors. The questionnaire will be administered to participants through face-to-face interviews conducted by trained research personnel in a private and confidential setting at the Vietnam National Lung Hospital.

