### Exclusion criteria

Participants will be excluded from the study if they decline to give informed consent to participate in the study or if they are hypersensitive or contraindicated to TST or IGRA.

#### Groups 2 and 3

Presumed TB disease with symptoms (cough, fever, night sweats, unintentional weight loss) and/or an abnormal CXR result suggestive of TB disease.Diagnosed with TB (microbiologically or clinically confirmed) in all forms or report having taken treatment for TB disease.History of TB infection (self-record or documented).

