### Data analysis plan

Points estimates of sensitivity and specificity with 95% CI will be calculated based on Wilson score methods to accommodate for the loss of coverage in small samples. The Cy-Tb and Standard F TB test index accuracy will be evaluated to fit with the case definition and results compared with the QFT-Plus reference standard test results presented in table 1.

**Table 1 T1:** The case definition and results

	Definitions			
Test results		Tuberculosis infection	Not infected	Total
	Detected	True positive	False positive	True positive+false positive
	Not detected	False negative	True negative	False negative+true negative
	Total	True positive+false negative	False positive+true negative	Total

Concordant with the methods employed in a systematic review by WHO, we consider the rate of negative results to represent proxy specificity regardless of TB incidence and estimates.^20^ Differences in proportion of negative results between investigated tests and the reference test will be calculated. In addition, we will also calculate the rate of negative results on the Cy-Tb and Standard F TB tests among QFT-Plus negative participants.

Sensitivity is the percentage of participants with positive study tests among those with microbiologically confirmed TB (group 1).

Specificity is the percentage of participants with negative study tests among those at low risk for TB infection (group 3). We will also calculate the proportion of people with negative index tests among those at risk for TB infection (group 2).

The descriptive statistics will be calculated for the sample and the contingency table will be created to evaluate the diagnostic performance, including sensitivity, specificity and associated 95% CI for the Cy-Tb test and Standard F TB assay in comparison with the reference standard. The area under the curves, that is, areas under the receiver-operating characteristics curve will be calculated to estimate the comparative diagnostic accuracy of the Cy-Tb test and Standard F TB assay and QFT-Plus.

Multiple multivariate logistic regression models will be performed to adjust for confounders while analysing associations between participants characteristics and test accuracy. Subgroup analysis of test accuracy in different groups will be done with regard to gender, age, BMI, comorbidities, TB exposure, etc.

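### BMI, a planned subgroup factor, is to be self-reported with records only as a supplement, although every participant is seen in person and could be weighed and measured

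*Protocol article*

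**What the plan says.** In the protocol article, the Data collection section lists, among other items, "body mass index (BMI), TB symptoms, TB exposure and previous TB disease or TB infection". These items "will be acquired through a preformed questionnaire during study visits". Their source is then given: "These data will be self-reported by participants and supplemented, where available, from the national TB registry and medical records". The setting is in person: "The questionnaire will be administered to participants through face-to-face interviews conducted by trained research personnel", at the Vietnam National Lung Hospital. Laboratory procedures describes a baseline visit followed by blood collection. No section mentions weighing participants or measuring their height.

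The Data analysis plan gives BMI an analytic role: "Subgroup analysis of test accuracy in different groups will be done with regard to gender, age, BMI, comorbidities, TB exposure, etc". It also states: "Multiple multivariate logistic regression models will be performed to adjust for confounders while analysing associations between participants characteristics and test accuracy". Sensitivity is defined there in Group 1, the patients with confirmed pulmonary TB. The Exclusion criteria for Groups 2 and 3 name the TB symptoms as "cough, fever, night sweats, unintentional weight loss".

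**The concern.** BMI is one of five factors named for the subgroup analysis. Unlike exposure history, it can be measured objectively on the spot. The article nevertheless makes self-report the main source, adds records only when they exist, and gives no rule for which value counts when the two disagree.

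The error may also run in one direction. The protocol treats unintentional weight loss as a sign of TB, and the people it excludes on that ground come from Groups 2 and 3 only. Recent weight loss is therefore most likely in Group 1, which supplies sensitivity. A patient who quotes a weight from before the illness overstates current BMI and may be counted as normal weight. If low BMI goes with a weaker test response, moving such patients into the normal-BMI stratum lowers its apparent sensitivity and narrows the contrast. At stake is the reading of the BMI subgroup and of the BMI term in the regressions.

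**Working it through.** The plan states no figure for a BMI effect, so none can be reproduced. What follows is an illustration.

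**What Group 1 was sized for.** The Sample size section uses overall sensitivities of 75.8% and 88.9% with precision 0.1. By n = z²·Se·(1−Se)/d²:
- Cy-Tb: 1.96² × 0.758 × 0.242 / 0.01 = 70.5, rounded up to 71.
- Standard F TB: 1.96² × 0.889 × 0.111 / 0.01 = 37.9, rounded up to 38.

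Both match the stated numbers, before any drop-out allowance. The target is overall sensitivity; nothing is sized for a BMI contrast.

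**Can an outdated weight change the category?** Assume a 5 kg loss not reflected in the reported weight, a height of 1.62 m and a cut-off of 18.5. None of these is in the document. The overstatement is 5 / 1.62² = 1.91 BMI units, so a true BMI of 17.0 is recorded as 18.9.

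**How far would the contrast shrink?** Group 1 has 100 patients (Study population). Assume 40 are truly underweight with sensitivity 65% and 60 are not, with sensitivity 83%. These values average to 0.4 × 65% + 0.6 × 83% = 75.8%, the protocol's Cy-Tb figure, but the split itself is assumed. Let a fraction m of the underweight be recorded as normal, regardless of test result. The apparent normal-BMI sensitivity is (60 × 0.83 + 40m × 0.65) / (60 + 40m), and the underweight stratum stays at 65%.

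| m | Apparent normal-BMI sensitivity | Apparent difference | Loss from 18 points |
|---|---|---|---|
| 0.2 | 55.0/68 = 80.9% | 15.9 points | 2.1 |
| 0.3 | 57.6/72 = 80.0% | 15.0 points | 3.0 |
| 0.4 | 60.2/76 = 79.2% | 14.2 points | 3.8 |

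**Against sampling error.** With perfectly measured BMI, the standard error of the difference is √(0.65 × 0.35/40 + 0.83 × 0.17/60) = 0.090, so the 95% half-width is 1.96 × 0.090 = about 17.6 points. A loss of 2.1 to 3.8 points is under a quarter of that.

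**Other assumptions.** Take sensitivity 60% in low BMI and 80% otherwise, a low-BMI share of 20% to 40%, and m from 10% to 50%. The true 20 points become between 19.5 (share 20%, m = 10%) and 15.0 (share 40%, m = 50%), so 98% to 75% of the contrast is kept. Power for the contrast is 47% to 59% with no misclassification and 27% to 29% at m = 50%. The direction is always attenuation. The estimate moves modestly; power suffers more if misreporting is common.

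**The case against.** The strongest reply is that the point rests on one blanket sentence in a condensed article. That sentence covers a mixed list, and BMI is a derived value; staff may in fact weigh participants, with the detail held in the case report form. This is possible, and if so a one-line correction settles the matter. It does not remove the point, because the article is not silent: it names a source for BMI, and that source is self-report.

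Second, records already supplement self-report, and Group 1 patients, enrolled at the hospital, are the ones most likely to have a chart. This stands as mitigation. It is not a guarantee, and no order of priority is given.

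Third, nothing in the document shows that patients quote a pre-illness weight, that low BMI weakens the test response, or that a particular BMI cut-off will be used. This stands in full: the mechanism is plausible but inferred, and every magnitude above is assumed.

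Fourth, the BMI contrast would be imprecise even with perfect measurement. This also stands, and it is why the point is minor.

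A reader might go further and infer that BMI adjustment would be uneven across the three groups. The document does not support that. Sensitivity is defined within Group 1 and specificity within Group 3, no BMI-adjusted comparison between groups is stated, and the regressions are not said to pool the groups.

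**Conclusion.** The point holds as a low-cost improvement. The protocol article states that a planned subgroup factor is self-reported, with records used only when they exist, in a study where every participant is physically present. The likely consequence is some misclassification of BMI and a modest attenuation of any BMI contrast in sensitivity: about 2 to 4 points of an assumed 18, well within the subgroup's sampling error. That size depends on the assumed underweight share, the assumed sensitivities in the two strata and 20% to 40% one-way misreporting, none of which can be derived from the document.

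It would be wrong to infer that the main results are compromised. The primary and secondary endpoints are sensitivity and specificity estimates that do not use BMI, so they are unaffected.

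**What to change.** Amend the Data collection section so that study staff measure weight and height at the baseline visit and BMI is computed from those values. Self-report would then remain the source for the history items only.

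The study was scheduled for April to December 2024, so some or all baseline visits may have passed. For those participants, give the charted weight nearest to blood collection priority over self-report. In all cases record whether each BMI value is measured, charted or self-reported, so that the BMI subgroup results can be read with the source in view. If BMI is already measured in practice, it is enough to correct the sentence.

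The cost is about two minutes per participant at an existing visit and one change to the case report form, with no extra staff or visit.
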